### Writing weekly feedback messages

If possible, the weekly feedback should be sent regularly every Monday. If the participant happens to ask a question around this time, then the response to that question can be combined with the weekly feedback.

The feedback should generally have the following elements (see below). However, individual circumstances might require you to add or omit some parts, as you deem appropriate. You should not always write exactly the same words or sentence. Even the order of these elements does not have to follow a rigid, inflexible pattern; use your own clinical judgment.

1. Brief hello (e.g., "Hello Michael,")
2. Acknowledge and reinforce effort. Examples:
  - "It was great to see that you worked through the first two chats!"
  - "I saw that you spent a lot of time with the program this week. That's really good!"
  - "Congratulations! You've now completed eight of the chats – that's quite an accomplishment!"
3. Acknowledge that they may not have used the program and encourage use. Example:

- “I noticed that you did not have a chance to work with the online program this week – that’s perfectly fine! I also hope that you were able to use some of the ideas and techniques from previous chats in your daily life, though!”
4. Provide feedback regarding mood/symptom course (optional, or if you notice something unusual in the mood/symptom trajectory).
    - For example:
      - “I was happy to see that your mood really improved over the last few weeks!”
      - It might be useful to ask questions that encourage reflection: “Why do you think that might be? What was it that made a positive difference?”
      - Another example: I saw that your mood went down quite a bit. What do you think might be the reasons for that? Don’t hesitate to write to me if there’s any way I can support you.
  5. Provide feedback regarding the content of the completed chats and emphasis on importance of continuous practice (check which chats have already been completed; if needed, refer to the attached overview of topics).
    - For example: “I hope that the chat about the relationship between negative thoughts and depression was helpful! It’s important to try to notice these thoughts now, and to challenge them. The worksheet on identifying and challenging negative thoughts could help you practice this.”
    - Alternatively, if a patient never writes anything proactively, you could ask a question to engage them: “How did you get on with the relaxation exercises? Were you able to do them and possibly try them out in your daily life?”
  6. Remind the patient about the next chat.
    - For example: “You can start with the next chat if you’d like. This one will deal with negative thoughts, and how they can sometimes maintain depressive moods.”
  7. The last point to note in your weekly message is that you’re available for questions.
    - For example: “Please don’t hesitate to get in touch with me if you have any questions or comments” or “If you have any questions or concerns, I’ll be happy to help you!”

### Example of Complete Message

Combining all the elements described above, a complete weekly message could look like this, for example:

Dear XXX,

It was great to see that you worked through the first two chats, and that your mood seems to have improved a little! I hope you found the relaxation exercises useful got something out of the chat dealing with negative thoughts. It'll be important now to apply the techniques you learned about in your daily life. For example, you could try to identify and challenge negative thoughts you notice. The worksheet might help you with that. You can find this worksheet in your area in the program's menu. Whenever you're ready, feel free to get started with the next chat, which focuses more on acceptance and learning to maintain a relaxed attitude.

Please don't hesitate to contact me if you have any questions or comments about anything. Best wishes, YOUR NAME HERE

### MS-specific feedback and responses to queries

- The general suggestion is NOT to give specific advice regarding which medication to take or not to take, which other treatment to pursue, etc.
- Therapists should validate the concern or question and encourage the patient to discuss any specific aspects of disease management with their doctor or treatment team.
- In case of other specific questions, it's recommended to consult with the study team, particularly with [name].

## List of Abbreviations

|              |                                                |
|--------------|------------------------------------------------|
| AE           | Adverse Event                                  |
| ANCOVA       | Analysis of Covariance                         |
| BDI-II       | Beck Depression Inventory – II                 |
| BICAMS       | Brief Cognitive Assessment in MS               |
| BVMT-r       | Brief Visuospatial Memory Test-revised         |
| CFS          | Chalder Fatigue Scale                          |
| CI           | Confidence Interval                            |
| CVLT-II T1-5 | California Verbal Learning Test-II             |
| EDSS         | Expanded Disability Status Scale               |
| FAS          | Full Analysis Set                              |
| FSMC         | Fatigue Scale for Motor and Cognitive          |
| ITT          | Intention-To-Treat                             |
| LOCF         | Last Observation Carried Forward               |
| MADRS        | Montgomery-Asberg Depression Rating Scale      |
| MDD          | Major Depressive Disorder                      |
| MI           | Multiple Imputation                            |
| M.I.N.I.     | Mini-International Neuropsychiatric Interview  |
| mITT         | modified Intention-To-Treat                    |
| MS           | Multiple Sclerosis                             |
| MSIS-29      | Multiple Sclerosis Impact Scale-29             |
| SAE          | Serious Adverse Event                          |
| SAP          | Statistical Analysis Plan                      |
| SBQ-R        | Suicide Behaviors Questionnaire – Revised      |
| SDMT         | Symbol Digit Modalities Test                   |
| SS           | Safety Set                                     |
| SUSAR        | Suspected Unexpected Serious Adverse Event     |
| WHO          | World Health Organization                      |
| WHO-QoL BREF | World Health Organization Quality of Life BREF |
| WLC          | Waitlist Control Group                         |
| PDDS         | Patient Determined Disease Steps               |

## 1 Introduction

This document has been written based on information contained in the trial protocol version 1.1, 02/2017. It describes the analysis after the first 12 weeks. The analysis after 12 months will be listed in a second Statistical Analysis Plan (SAP).

### 1.1 Background and Rationale

Depression is the most common comorbidity of Multiple Sclerosis (MS). However, depression remains underdiagnosed and there are no treatments with proven effectiveness from large (phase III) trials. In addition, symptoms of MS such as mobility issues, cognitive impairment and fatigue make it difficult for MS patients to travel to and attend regular psychotherapy. Effective treatment options are therefore needed. The internet-based program “Deprexis”, developed by GAIA group in Hamburg/Germany could facilitate access to treatment and has shown promising results in a small monocentre study in Germany for MS patients (1). Deprexis is an online tool and consists of 10 sequential modules plus an introduction and a summary module. Deprexis implements the technique of simulated dialogue by giving the user multiple choice options and tailoring the subsequent content to the patient’s responses. Thereby, the user’s responses determine the course of each module. The Deprexis program has been adapted from the generic version to improve suitability for use by patients with MS. This trial evaluates the effectiveness of MSDeprexis in an international multicentre trial. There are three treatment groups, one group uses only MSDeprexis for 12 weeks, the other group uses MSDeprexis with an added email support for 12 weeks and the third group is a waitlist control group (WLC).

### 1.2 Objective and endpoints

Table 1 Objectives and related endpoints

|                  | Objective                                                                | Endpoint                                                                                                                       | Measurement time points                                                    |
|------------------|--------------------------------------------------------------------------|--------------------------------------------------------------------------------------------------------------------------------|----------------------------------------------------------------------------|
| Primary   | Assessment of depressive symptoms after intervention              | Beck Depression Inventory – II (BDI-II)                                                                                        | V1 (baseline), I1 (after 4 weeks), I2 (after 8 weeks), V2 (after 12 weeks) |
| Secondary | Assessment of quality of life after intervention                  | World Health Organization Quality of Life BREF (WHO-QoL BREF) and the Multiple Sclerosis Impact Scale (MSIS-29) after 12 weeks | V1 (baseline), V2 (after 12 weeks)                                         |
|                  | Assessment of fatigue after intervention                          | Fatigue Scale for Motor and Cognitive Functions (FSMC) and the Chalder Fatigue Scale (CFS) after 12 weeks                      | V1 (baseline), V2 (after 12 weeks)                                         |
|                  | Assessment of the percentage of patient with a clinical diagnosis | M.I.N.I. structural clinical interview after 12 weeks                                                                          | V1 (baseline), V2 (after 12 weeks)                                         |

|               | Objective                                                            | Endpoint                                                                                                                                                                      | Measurement time points            |
|---------------|----------------------------------------------------------------------|-------------------------------------------------------------------------------------------------------------------------------------------------------------------------------|------------------------------------|
|               | of current major depressive disorder (MDD) after intervention |                                                                                                                                                                               |                                    |
|               | Assessment of severity of depression after intervention       | Clinician-rated Montgomery-Asberg Depression Rating Scale (MADRS) after 12 weeks                                                                                              | V1 (baseline), V2 (after 12 weeks) |
| Safety | Assessment of suicidal ideation                                      | Suicide Behaviors Questionnaire – Revised (SBQ-R), predefined criterion for acute risk of suicide is response 3a or 3b on SBQ-R item 3 plus a score of 5 or 6 on SBQ-R item 4 | V1 (baseline), V2 (after 12 weeks) |

### 1.3 Primary objective and endpoint

To determine if MSDeprexis is effective for reducing **depressive symptoms** at the end of treatment (week 12), the Beck Depression Inventory – II (BDI-II)) in patients with MS is used and compared to the control group. Because the literature strongly suggests that therapist-guided internet-based interventions lead to better outcome MSDeprexis with an added email support (MSDeprexisPlus) is also compared to the control group after 12 weeks (MSDeprexis vs. WLC and MSDeprexisPlus vs. WLC).

### 1.4 Potential moderators

The level of disability measured by the Patient Determined Disease Steps (PDDS), the cognitive impairment measured by Symbol Digit Modalities Test (SDMT) and the level of fatigue measured by the FSMC will be investigated as potential moderators.

## 2 Study methods

### 2.1 Trial design

IDEMS is a three arm, randomized, controlled, international multicentre trial with five academic centres. Patients are randomized to one of the three treatment groups after informed consent. One group uses only MSDeprexis for 12 weeks, the other group uses MSDeprexis with an added email support for 12 weeks and the third group is a waitlist control group.

The potential of a booster session to enhance maintenance is analysed in patients who were randomized to either the MSDeprexis or the MSDeprexisPlus group. These patients will be re-randomized to receive additional booster session (see Figure 1). This analysis is not part of this SAP.

[figure not shown]

Figure 1: Trial Design Schematic and Treatment Plan.

## 2.2 Randomization

Patients are randomized 1:1:1 to one of the three trial arms. There is no blocking and no stratification. To ensure concealed allocation, eligibility is determined and all baseline assessments completed before randomization in compliance with CONSORT guidelines. The clinicians and raters who will be conducting clinical assessments (structured interviews) will be blind to treatment assignment (single blind RCT).

## 2.3 Sample Size

A sample size of 100 patients per intervention group gives a conjunctive power (probability of rejecting both null hypotheses comparing MSDeprexis and MSDeprexisPlus to waitlist control) of 90% for a Dunnett test at the usual one-sided significance level of 2.5% assuming standardized mean differences of 0.5 for MSDeprexis vs. WLC and 0.8 for MSDeprexisPlus vs. WLC in the primary outcome change in BDI from baseline to week 12. Adjusting for 20% dropout we aim to recruit 125 patients per group resulting in a total sample size of 375 patients. The power was simulated with 10,000 replications using EAST 6.3.

## 2.4 Framework

The superiority of MSDeprexis compared to a waitlist control group is analysed. Specifically, the use of MSDeprexis only as well as the use of MSDeprexis with an added email support are compared to the control group.

## 2.5 Statistical Interim Analyses and Stopping Guidance

No interim analyses or guidelines for stopping the trial early are planned. There are no predefined stopping rules.

## **2.6 Timing of the Final Analysis**

All outcomes are analysed collectively after the last patient has completed the visit after 12 weeks. In addition, to explore the long-term stability of therapeutic effects and the potential of a booster session to enhance maintenance another evaluation takes place after 12 months (not part of this SAP).

## **2.7 Timing of Outcome Assessments**

Outcomes are measured at week 0 (baseline) and week 12 when visiting the clinic. In addition, BDI-II outcomes are measured at week 4 and 8 in online assessments. Follow-up visits for all patients who want to use MSDeprexis after 6 and 12 month are conducted online.

# **3 Statistical Principles**

## **3.1 Confidence intervals and p-values**

If not specified otherwise, tests will be performed two-sided with a significance level of 5% and 95% confidence intervals (CI) will be provided for parameter estimates. For the primary analysis, MSDeprexis vs. WLC and MSDeprexisPlus vs. WLC will be tested by a Dunnett test controlling the familywise type I error rate at the level of 2.5% (one-sided).

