## 5.2 Analysis methods

### Primary endpoint

The primary outcome change in BDI from baseline to week 12 will be analysed by means of linear mixed effects models for repeated measures adjusted for baseline measurements with fixed effects for intervention, region (US, GER), time and baseline BDI score, and random subject effects for individual patients including all patients with at least one post-baseline measurement (13). Least squares means will be reported for the intervention groups with 95% CI as well as the difference between the least squares group means with 95% CI. MSDeprexis vs. WLC and MSDeprexisPlus vs. WLC will be tested by a Dunnett test controlling the familywise type I error rate at the level of 2.5% (one-sided). The primary hypothesis will be tested in a confirmatory manner:

$H_0^{(1)}: \mu_{WLC} \leq \mu_{Dep}$  vs.  $H_1^{(1)}: \mu_{WLC} > \mu_{Dep}$  and  $H_0^{(2)}: \mu_{WLC} \leq \mu_{DepPlus}$  vs.  $H_1^{(2)}: \mu_{WLC} > \mu_{DepPlus}$ , with  $\mu_{WLC}$ ,  $\mu_{Dep}$  and  $\mu_{DepPlus}$  being the means of the change in BDI from baseline to week 12.

In a secondary step, the added value of therapist email support MSDeprexis vs. MSDeprexisPlus at a two-sided level of 5%, if efficacy of MSDeprexis and MSDeprexisPlus for reducing depressive symptoms in MS could be demonstrated, will be determined.

SAS analysis:

```
proc mixed data =_data_t;
class group time region;
model score = group time group*time baseline baseline*time region / s ddfm=kr;
repeated time / subject=id type=un;
lsmeans group / adjust = dunnett;
```

In a sensitivity analyses last observation carried forward (LOCF) and multiple imputations (MI) will be used to deal with missing values for the BDI-II score (missing visits) and for each method an analysis of covariance (ANCOVA) for the BDI-II score after 12 weeks is carried out with BDI-II score at baseline as covariate.

In an exploratory analysis trends in the utilization time of MSDeprexis [number of days with activity within the program] in both intervention groups will be investigated.

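### Single-step Dunnett is valid, but step-down Dunnett would raise power to reject both primary nulls from about 90.5% to 94.1% at the same familywise error

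*Supplement*

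**What the plan says.** SAP 3.1 and 5.2 state that MSDeprexis versus waitlist and MSDeprexisPlus versus waitlist "will be tested by a Dunnett test controlling the familywise type I error rate at the level of 2.5% (one-sided". Protocol 12.5.1 and 12.5.2 say the same. None of these sections mentions a step-down or closed procedure, and the SAS statement in SAP 5.2 uses `adjust = dunnett`, which is the single-step adjustment.

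SAP 2.3 sets the size on conjunctive power: "probability of rejecting both null hypotheses comparing MSDeprexis and MSDeprexisPlus to waitlist control) of 90% for a Dunnett test", "assuming standardized mean differences of 0.5 for MSDeprexis vs. WLC and 0.8 for MSDeprexisPlus vs. WLC". The figure is for 100 patients per group. Dropout is then added: "Adjusting for 20% dropout we aim to recruit 125 patients per group resulting in a total sample size of 375 patients". SAP 2.2 gives the allocation: "Patients are randomized 1:1:1 to one of the three trial arms".

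SAP 5.2 lists the two nulls as separate confirmatory hypotheses. It tests MSDeprexis against MSDeprexisPlus at two-sided 5% only "if efficacy of MSDeprexis and MSDeprexisPlus for reducing depressive symptoms in MS could be demonstrated".

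**The concern.** Single-step Dunnett applies one critical value, about 2.22, to both comparisons. It keeps that value for the second comparison even after the first null has been rejected. At 297 degrees of freedom, 2.22 corresponds to a one-sided level of about 1.35% for a single comparison. Once the larger statistic has passed 2.22, closed testing allows the remaining comparison the full one-sided 2.5%, a critical value of about 1.97.

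This matters most for rejecting both nulls. Under the plan's assumptions the guided arm (0.8) is almost certain to be rejected, so the unguided arm (0.5) decides whether both are. That comparison is held to a stricter level than familywise control requires. The price falls on the criterion the trial was sized on and on the gate to the guided-versus-unguided test.

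**Working it through.** **Inputs.** From SAP 2.2, 2.3 and 3.1: n = 100 completers per arm, allocation 1:1:1, standardised differences 0.5 and 0.8, familywise error 2.5% one-sided. A shared control with equal arms gives the two statistics a correlation of 0.5. With simple t-statistics and pooled variance, df = 3 × 99 = 297.

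**Critical values.** One-sided 2.5% Dunnett with two comparisons: 2.223 (numerical integration). One-sided 2.5% for a single t-test: 1.968.

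**Noncentrality, d × √(n/2).** Unguided: 0.5 × √50 = 3.536. Guided: 0.8 × √50 = 5.657.

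**The plan's own figure.** Single-step rejects both nulls if both statistics exceed 2.223.
- Guided: probability 99.97%.
- Unguided: probability 90.5% (normal approximation: 3.536 − 2.223 = 1.313, and Φ(1.313) ≈ 0.905).
- Both, by simulation (4 million draws): 90.5%, or 90.7% with normal instead of t critical values.

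This reproduces the stated 90%.

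**Step-down.** Reject both if the larger statistic exceeds 2.223 and the smaller exceeds 1.968. The unguided comparison now has probability 94.1% (approximation: 3.536 − 1.968 = 1.568, and Φ(1.568) ≈ 0.94). Both, by simulation: 94.1%. The gain is about 3.6 points, and the chance of missing at least one null falls from 9.5% to 5.9%. The chance of at least one rejection is 99.98% under either rule, because both start with the same comparison.

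**Familywise error of step-down, simulated.**

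| True effects | Step-down | Single-step |
|---|---|---|
| 0 and 0 | 2.49% | 2.49% |
| 0 and 0.3 | 2.35% | 1.34% |
| 0 and 0.8 | 2.51% | 1.34% |
| 0.5 and 0 | 2.49% | 1.35% |

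All step-down values are at or below 2.5% within simulation error. Theory says the same: under closed testing a null is rejected only if the intersection hypothesis (2.223 on the larger statistic) and its own test (1.968) both reject.

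**How the gain moves.** Only the first row uses the plan's figures. The others are assumptions that show the range.

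| Completers per arm | Effects | Single-step | Step-down |
|---|---|---|---|
| 100 | 0.5 / 0.8 | 90.5% | 94.1% |
| 100 | 0.4 / 0.8 | 72.7% | 80.5% |
| 100 | 0.5 / 0.5 | 84.0% | 89.5% |
| 80 | 0.5 / 0.8 | 82.5% | 88.2% |
| 110 | 0.5 / 0.8 | 93.1% | 95.9% |
| 125 | 0.5 / 0.8 | 95.8% | 97.6% |

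At 0.5 / 0.8, step-down reaches 90% with about 85 completers per arm and single-step with about 99.

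**The case against.** **Nothing here is wrong.** Single-step Dunnett controls the error, meets the 90% target and is named consistently in both documents. This stands in full: the point is an improvement, not a correction.

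**A reader might infer that the trial succeeds only if both nulls are rejected.** The documents do not say so. Conjunctive power is a sizing criterion, the both-arms condition gates only the guided-versus-unguided test, and SAP 5.2 lists two separate confirmatory nulls. If both rejections were strictly required, no multiplicity adjustment would be needed: two plain one-sided 2.5% tests, both required, also give 94.1%. The case for step-down does not rest on that reading. If either null can support a claim on its own, step-down leaves the chance of at least one rejection unchanged and raises the chance of both.

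**Intervals.** SAP 5.2 promises 95% intervals for the group differences. Single-step Dunnett has directly matching simultaneous intervals; step-down has no simple counterpart. Preferring agreement between test and interval to about 3.6 points of power is a legitimate choice. This stands as the real cost.

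**Size.** The calculation uses simple t-statistics on completers. The planned analysis is a baseline-adjusted repeated-measures model that keeps everyone with at least one post-baseline score. If that is worth 110 to 125 completers per arm (an assumption; the documents give no correlation), the gain falls to 2.8 or 1.8 points. At the effects protocol 2.1 cites from the earlier three-arm study (0.66 and 1.14), both methods exceed 99%. Against this, protocol 2.1 also cites 0.36 and 0.46 for the program in other trials, and smaller effects for the unguided arm, such as the 0.4 tabulated above, enlarge the gain.

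**Timing.** SAP 5.3 already reports five missing baseline assessments, so data had been collected when it was written. A more liberal primary rule adopted at that stage needs a documented reason and must precede any view of outcomes by arm.

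**Conclusion.** The point holds as a missed efficiency. As a test, step-down Dunnett dominates the planned procedure: it never rejects less, sometimes rejects more, and keeps the same strong one-sided 2.5% familywise control. At the planning assumptions the gain in conjunctive power is about 3.6 points (90.5% to 94.1%) with no extra patients or data. That size depends on effects of 0.5 and 0.8, 100 completers per arm, equal allocation and simple t-statistics. The dominance and the error control do not depend on the effect sizes. The documents do not support calling the present plan invalid, underpowered or in breach of its own success rule. The change is worth making because it is cheap and acts on the criterion used to size the trial.

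**What to change.** Before outcomes are unblinded, in SAP 3.1 and 5.2 and the matching wording in protocol 12.5.1 and 12.5.2:

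1. Specify step-down Dunnett on the two week-12 contrasts. Compare the larger statistic with the one-sided 2.5% Dunnett critical value (about 2.22). If it is rejected, test the other at one-sided 2.5% (about 1.97). If it is not, stop.
2. Keep the gate to MSDeprexis versus MSDeprexisPlus as it is.
3. Say which intervals are reported. If single-step simultaneous intervals are given, note that in borderline cases one may include zero although the step-down test rejects. If plain 95% intervals are given, label them unadjusted: read as tests, the pair carries a one-sided familywise error of about 4.5%.
4. In SAP 2.3 and the protocol's sample size text, note that the 90% was computed for the single-step test and is conservative for the step-down rule. The sample size need not change.

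The cost is a short amendment to both documents, a few lines of code for the second step, and the loss of simple matching simultaneous intervals. If outcomes by arm have already been seen, the single-step test should remain the confirmatory one.
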